### Support

In the intervention conditions, the participants will receive human and ICT support.

Regarding human support, one trained predoctoral student in our group will make several brief phone calls at four points in time:*An initial telephone session:* to explain the characteristics of the RCT to the participant and administer the clinical diagnostic interview and find out whether s/he fulfills the inclusion criteria.*An initial phone call in the “Welcome” module*: encouraging patients to start the program, do one module every 2 weeks, and do the homework tasks in each module. This phone call will take place when the participants do the pre-treatment assessments.*One brief phone call (maximum of 10 min) when the participants reach the mid-point of the intervention (module 4)*: 1) to ask the participants about any doubts or difficulties regarding the use of the program and help them; 2) to remind them that they can review the content of each module; 3) to emphasize the importance of doing the tasks in each module and practice the strategies they learn; 4) to motivate patients to continue with the program and positively reinforce them for engaging in the intervention; and 5) to remember that the best way to experience the intervention is by doing one module every 2 weeks.*A final phone call after the post-assessment:* to ask them their qualitative opinion about the intervention and remind participants that they will be allowed to use the intervention program any time they want to during the study period, and that we will contact them to do the follow-up assessment.

ICT support will consist of multiple-choice questions about the module’s contents in order to provide the participant with the correct feedback for their responses and a detailed explanation. Furthermore, the participants will receive an automated email encouraging them to continue with the modules if they have not accessed the program for a week. In addition to this automated support, the program offers continued feedback to users through the transversal tools described earlier.

### Instruments

#### Diagnostic interview

Mini International Neuropsychiatric Interview Version 5.0.0 (MINI) [61]. It is a structured diagnostic interview for DSM-IV and ICD-10 psychiatric disorders. It was designed to be used by clinicians or even by nonclinical personnel after brief training, and it has an administration time of approximately 15 min. The MINI has excellent interrater reliability (K = .88–1.00), and it has been translated and validated in Spanish [62].

#### Primary outcomes

##### Depression

Beck Depression Inventory (BDI-II) the BDI-II is a 21-item self-report multiple-choice inventory that is widely used to detect and assess the severity of depressive symptoms. The items, scored on a scale from 0 to 3, cover the different symptoms characterizing major depression disorder in the DSM-IV [57], such as sadness, pessimism, past failure, loss of pleasure, guilty feelings, punishment feelings, suicidal thoughts or wishes, etc. The scores on the scale range from 0 to 63. The internal consistency of the BDI-II is high (alpha = 0.76 to 0.95), and for the Spanish version of the instrument (alpha = 0.87), for both general and clinical populations (alpha = 0.89) [63].

##### Positive and negative emotionality

Positive and Negative Affect Scale (PANAS) the PANAS [64] consists of two 10-item mood scales that assess two independent dominant dimensions of affective structure: positive affect (PA) and negative affect (NA). Each scale ranges from 10 to 50. The PANAS is brief, reliable, and has shown excellent internal consistency (alpha between 0.84 and 0.90) and convergent and divergent validity. The Spanish version has also shown high internal consistency (α = 0.87 and 0.89 for PA and NA in men, respectively, and α = 0.89 and 0.91 for PA and NA in women, respectively [64].

##### Secondary outcomes and post-module measures

Connor-Davidson Resilience Scale (CD-RISC) the CD-RISC [65] is a brief scale that consists of 25 items. The person must indicate to what extent each statement has been true for him/her in the past month on a scale from 0 to 4, where 0 =“has not been true at all” and 4=“true almost always”. The total scores range from 0 to 100; higher scores indicate greater resilience. Previous studies have shown that the CD-RISC has good internal consistency (Cronbach alpha above 0.70) [65].

##### Overall Depression Severity and Impairment Scale (ODSIS)

The ODSIS [66] is a brief, 5-item self-report measure for assessing the frequency and severity of depression, as well as functional impairments in pleasurable activities, work or school interference, and social relationship interference associated with depression. The items are scored on a scale from 0 to 4, and they function similarly across clinical and nonclinical samples. The ODSIS has shown excellent internal consistency (Cronbach’s alpha between .91 and .94) and good convergent/discriminant validity [66].

##### Perceived Stress Scale (PSS)

The PSS [67] is a self-report instrument that assesses the level of stress perceived in the past month. It consists of 14 items scored on a scale ranging from 0 (never) to 4 (very often). The total score range varies between 0 (minimum perceived stress) and 56 (maximum perceived stress). In the present study, a 4-item PSS (PSS-4) was used. This PSS-4 was introduced as a brief version for situations requiring a very short scale or telephone interviews [68]. It has been validated in different studies, showing an internal consistency reliability of 0.76–0.82 [69].

##### Overall Anxiety Severity and Impairment Scale (OASIS)

The OASIS [70] is a 5-item self-report measure, rated from 0 to 4, that can be used to assess the frequency and severity of anxiety disorders, multiple anxiety disorders, and subthreshold anxiety symptoms. The scale also provides measures of functional impairments in pleasurable activities, work or school interference, and social relationship interference associated with anxiety symptoms. The OASIS has demonstrated strong psychometric properties with good internal consistency (alpha = 0.80), test-retest reliability (K = 0.82), and convergent validity [70–72].

##### Quality of life Inventory (QLI)

The QLI [73] is a brief self-report questionnaire used to measure the perceived quality of life in different areas. The inventory consists of 10 items scored on a scale ranging from 1 to 10. It is calculated by averaging the 10 items, and the maximum score is 10. The QLI assesses aspects related to physical well-being, psychological well-being, self-care and independent functioning, occupational functioning, interpersonal functioning, social emotional support, community and services support, personal fulfillment, spiritual fulfillment, and overall quality of life. The QLI has shown excellent internal consistency (between 0.90 and 0.92), test-retest reliability (0.87), and discriminant validity. The Spanish validation of the QLI [74] has also demonstrated good test-retest reliability (0.89) and discriminant validity.

##### Pemberton Happiness Index (PHI)

The PHI [75] is a brief instrument to measure different domains of well-being (i.e., general, hedonic, eudemonic, and social). It contains 11 items rated on a scale where 0 = strongly disagree and 10 = strongly agree. The reliability of this scale is quite satisfactory (alpha = 0.89) [75].

##### Enjoyment Orientation Scale (EOS)

The EOS [76] is a 6-item self-report measure that assesses the extent to which participants try to be receptive and make an effort to be engaged in pleasant things (anticipatory pleasure). This scale is very related to the behavioral activation system that is believed to regulate appetitive motives. The items on the EOS are rated on a Likert scale from 1 (“strongly disagree”) to 7 (“strongly agree”) [76].

##### Environmental Reward Observation Scale (EROS)

The EROS [77] is a brief, reliable, and valid measure of environmental reward. It consists of a 10-item Likert measure rated from 1 (“strongly disagree”) to 4 (“strongly agree”), with the total score representing the sum of the 10 items. The Spanish EROS is internally consistent (alpha = 0.86) and valid [77].

##### Acceptance, satisfaction and usability outcomes

Expectation of treatment scale and opinion of treatment scale these two scales are adapted from Borkovec and Nau [78]. Each scale contains 5 items, regarding whether the treatment is logical, treatment satisfaction, the treatment’s utility for other psychological problems, and the treatment’s usefulness for the patient’s specific problem. The expectation scale is administered at the post-module 2 assessment, when the treatment has been explained to the participants, and the opinion scale is administered at the end of the treatment, with the aim of assessing satisfaction. Our group has used this questionnaire in several research studies [51, 79].

**System Usability Scale (SUS)**

The SUS [80] is a brief, reliable scale for measuring the usability of a program. It consists of a 10-item questionnaire with 5 response options, from 0 (“strongly disagree”) to 4 (“strongly agree”). Its purpose is to collect the user’s opinion about the usability of the system, and unacceptable usability may indicate that the user has had technical difficulties with the program. The SUS adjective rating scale (from “Worst imaginable” to “Best imaginable”) will be used to provide a qualitative comparison of usability scores [81].

The study measures and area and time of assessment are summarized in Table 4.

**Table 4 Tab4:** Study measures, assessment area and time of assessment

Outcomes	Concept	Instrument	Time of assessment			
			BL	Post-T	Post-M	FUPs (3, 6, 12)
Diagnostic interview	Diagnosis	MINI Neuropsychiatric Interview	X	X		X
Primary	Depression	BDI-II	X	X		X
	Positive and Negative affect	PANAS	X	X	X	X
Secondary	Resilience	CD-RISC	X	X		X
	Depression	ODSIS	X	X	X	X
	Perceived Stress	PSS	X	X		X
	Anxiety	OASIS	X	X	X	X
	Quality of life	QLI	X	X		X
	- Well-being	PHI	X	X		X
	- Anticipatory pleasure	EOS	X	X		X
	- Environmental reward	EROS	X	X		X
	Acceptance, satisfaction and usability outcomes					
	- Expectation of treatment	Expectation of Treatment Scale	X			
	- Opinion of treatment	Opinion of Treatment Scale		X		
	- Usability	SUS		X		

Note: *BL* Baseline, *Post-T* Post-treatment, *Post-M Post Module*, *FUPs (3,6,12)* 3, 6, and 12-month follow-ups, *BDI-II* Beck Depression Inventory-II, *CD-RISC* Connor-Davidson Resilience Scale, *PANAS* Positive and Negative Affect Scale, *ODSIS* Overall Depression Severity and Impairment Scale, *PSS* Perceived Stress Scale, *OASIS* Overall Anxiety Severity and Impairment Scale, *QLI* Quality of Life Index, *PHI* Pemberton Happiness Index, *EOS* Enjoyment Orientation Scale, *EROS* Environmental Reward Observation Scale, *SUS* System Usability Scale

**Sample size and power calculations**

The a priori sample size determination was performed based on the main objective of this investigation. Following Cohen’s (1988) guidelines, we assumed a proportion of explained variance of low magnitude for the interaction between the type of intervention and the measurement occasion, that is, 0.01. For a significance level of 5%, statistical power of 80%, assumed sphericity, and correlation of .7 between repeated measures (following Rosenthal’s 1991 recommendation), the total sample size needed was 147 participants (49 per intervention group). To this figure, an additional 30% was added to anticipate potential dropouts. Therefore, the total sample size of the study was 192 participants (64 per intervention group). Sample size calculations were carried out with the statistical program G*Power 3.1.9.2 [82].

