**Methods:**

The current study will be a three-armed, simple-blinded, randomized controlled clinical trial with a dismantling design. 192 participants will be randomly assigned to: a) an Internet-based Global Protocol condition, which includes traditional therapeutic components of evidence-based treatments for depression (Motivation for change, Psychoeducation, Cognitive Therapy, Behavioral Activation (BA), Relapse Prevention) and PPs component, offering strategies to enhance positive mood and promote psychological strengths; b) an Internet-based BA Protocol condition (without the PPs component), and c) an Internet-based PPs Protocol condition (without the BA component). Primary outcome measures will be the BDI-II and PANAS. Secondary outcomes will include other variables such as depression, anxiety and stress, quality of life, resilience, and wellbeing related measures. Treatment acceptance and usability will also be measured. Participants will be assessed at pre-, post-treatment, 3-, 6- and 12- month follow- ups. The data will be analyzed based on the Intention-to-treat principle. Per protocol analyses will also be performed.

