### Statistical analysis

Per protocol and Intention-to-treat (ITT) analyses will be performed, following the CONSORT and CONSORT-eHealth recommendations [56, 83]. Between-group differences in baseline clinical and socio-demographic characteristics will be explored using analysis of variance (ANOVA) for continuous data, and chi-square tests (χ2) for categorical variables. Both normality and multinormality assumptions will be assessed by applying the Kolmogorov-Smirnov (K-S) test, skewness and kurtosis indexes, and histogram and Q-Q plots. Levene’s test will be conducted to check homoscedasticity assumptions for equality of variances, and Mauchly’s test to explore sphericity assumptions. Missing data patterns will be assessed, and whether missing data are missing completely at random (MCAR) will be checked with Little’s MCAR test [84]. The ITT principle will be applied for primary and secondary outcomes collected at post-treatment, and at the 3, 6, and 12-month follow-ups. In this regard, the maximum likelihood (ML) method using the Expectation Maximization (EM) algorithm will be used to deal with missing data, due to its flexibility in repeated-measures ANOVAs in handling missing data appropriately (i.e., [85, 86]. Nevertheless, several approaches will also be considered and assessed using sensitivity analyses in order to apply the most robust and adequate method based on both missing data patterns and literature recommendations (i.e., [87, 88]. Repeated analysis of variance (rm-ANOVA) will be performed to explore the main and interaction effects of the treatments on all the primary and secondary outcomes. Significant effects will be followed up by pairwise comparisons, such as the Tukey procedure when the homoscedasticity assumption is met, and the Games-Howell procedure if this assumption is not met. Effect sizes (Cohen’s *d*) and their respective 95% confidence intervals (95% IC) will be calculated and reported for within- and between-group comparisons, according to authors’ recommendations [89–91]. In addition to ITT analyses, per protocol analyses will also be conducted. It is true that these analyses suffer from selection bias, but they will allow us to reach conclusions about the efficacy of the treatment in patients who complete all the intervention modules [92].

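### The sample size rests on one interaction test at 5%, which reproduces as pre-post, but three primary scores are each tested with no control across them: a 10–14% chance of at least one false-positive primary interaction.

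*Protocol article*

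**What the plan says.** **Sizing.** In the protocol article, Sample size and power calculations, the assumed effect is a proportion of explained variance for "the interaction between the type of intervention and the measurement occasion, that is, 0.01". The other inputs are: "For a significance level of 5%, statistical power of 80%, assumed sphericity, and correlation of .7 between repeated measures". The result is 147 participants (49 per arm), raised by 30% to 192 (64 per arm). The section names neither the outcome nor the number of occasions.

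**Primary outcomes.** The Abstract states: "Primary outcome measures will be the BDI-II and PANAS". The section on positive and negative emotionality describes the PANAS as two separate scales, "positive affect (PA) and negative affect (NA"), each scored 10 to 50, and gives no total score. There are therefore three primary scores. Table 4 schedules them at baseline, post-treatment and 3, 6 and 12 months, which is five common occasions.

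**Analysis.** The Statistical analysis section applies a repeated-measures ANOVA, with main and interaction effects, to every primary and secondary outcome. The only multiplicity step it describes is this: "Significant effects will be followed up by pairwise comparisons, such as the Tukey procedure when the homoscedasticity assumption is met", with Games-Howell otherwise. It gives no hierarchy, no split of the 5% level, no rule that all scores must succeed, and no primary time point.

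**The concern.** The sample-size section and the analysis section describe different things. One justifies the sample with a single test at 5%. The other produces three primary interaction tests, each of which a reader would take at 5%.

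The aim of a dismantling trial is to say whether a component contributes. If any one of the three primary scores can carry that claim, the overall false-positive risk exceeds the 5% that the sample-size section names. Tukey or Games-Howell does not help here, because it protects the three arm pairs within one score and not the set of scores.

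There is also a question of what the 80% refers to. The questions of interest are Global against BA and Global against PPs, but the stated power belongs to the three-arm interaction, and the text does not say over how many occasions.

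**Working it through.** **Inputs.** From the sample-size section: explained variance 0.01, so f² = 0.01/0.99 = 0.0101; α = 0.05; ρ = 0.7; sphericity, so ε = 1. From the design: k = 3 arms. The number of occasions m is not stated there, so it is varied.

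**1. Reproducing 147.** For the within-between interaction in G*Power:

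- λ = f²·N·m·ε/(1 − ρ)
- df1 = (k − 1)(m − 1)ε
- df2 = (N − k)(m − 1)ε
- power from the noncentral F distribution

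At m = 2 and N = 147, λ = 0.0101 × 147 × 2/0.3 = 9.90 with df 2 and 144, and power is 80.3%.

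| Occasions | N for 80% (equal arms) | Power at 147 |
|---|---|---|
| 2 | 147 | 80.3% |
| 3 | 123 | 88.2% |
| 4 | 105 | 93.4% |
| 5 | 93 | 96.4% |

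So 147 is the pre-post figure. Five occasions with ε = 0.5 would also give 147, but that contradicts "assumed sphericity".

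**2. Error rate over three scores at 5% each.** If the scores are independent, 1 − 0.95³ = 14.3%. For correlated scores, three 2-df tests were simulated (400,000 draws): 12.6% at a correlation of 0.5, 11.1% at 0.7 and 10.0% at 0.8. A simulation of the full ANOVA with 49 per arm gave much the same for two and for five occasions: 11.3–11.4% at 0.7 and 10.4–10.7% at 0.8. Counting BDI-II and PANAS as only two independent tests still gives 1 − 0.95² = 9.75%.

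**3. Cost of a Bonferroni split** (0.05/3 per score, the strictest step in Holm). The figure 134 is 192 × 0.7, what remains after the planned loss.

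| Tests | Power at 147 | Power at 134 |
|---|---|---|
| Five occasions, ε = 1 | 91.6% | 87.8% |
| Five occasions, ε = 0.7 | – | 75% |
| Pre-post | 66.0% | 60.7% |

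A pre-post analysis with this split would need 192 evaluable participants for 80%.

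**4. What the planned effect means at two occasions.** Let d be the between-arm difference in change, in SD of a single measurement.

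- One arm apart from two equal arms: f² = d²/18, so d = √(18 × 0.0101) = 0.43.
- Equally spaced arms, d between the extremes: f² = d²/24, so d = √(24 × 0.0101) = 0.49.

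The variance of change is 2(1 − 0.7) = 0.6, so at 49 per arm the standard error of a contrast is √(2 × 0.6/49) = 0.156. Using the Tukey critical value and the noncentral t distribution, pairwise power is 64% for 0.43 SD and 78% for 0.49 SD.

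**The case against.** - **The 5% per score is inferred.** It is stated only in the sample-size section, and a rule across co-primary scores may sit in an analysis plan that is not shown. The article also allows its procedures to vary after a methods review. This limits the point: a missing rule alone would not be a finding. What stands is that the article justifies its sample with one test at 5%, fixes separate analyses for three scores, and describes adjustment for arm pairs only.
- **Five occasions might seem to add false positives.** They do not. The interaction over five occasions is still one F test per score.
- **The mismatch in occasions might seem to leave the trial short.** It does the reverse. With the stated inputs and five occasions, power is 96% at 147 and 94% at 134.
- **The low-magnitude label might seem wrong, given 0.43–0.49 SD.** It is not an error. The section follows Cohen's benchmark, under which 0.01 explained variance is small. The SD figure is useful extra information.
- **The dismantling contrasts might seem to fail a promise of 80%.** The article makes no such promise for pairs, and their power depends on the pattern of means (64% to 78%). It also plans effect sizes with 95% intervals, which would show imprecision.
- **Gating PANAS behind BDI-II at post-treatment might seem the natural remedy.** The documents do not favour it. Positive affect is a stated treatment target, and the follow-ups are part of objective (a).

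**Conclusion.** The point holds in a limited form. Followed as written, the plan carries a 10–14% chance of at least one false-positive primary interaction, against the single 5% in the sample-size section. The range assumes correlations between the scores from 0 to 0.8, which the documents do not give, and a claim of success on any one score. It would not apply if all three had to be significant, but no such rule is stated. Main effects, secondary outcomes and the per-protocol analysis lie outside this figure.

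That 147 is a two-occasion calculation is an inference from the stated inputs, though a firm one under sphericity. It leaves the sized test undefined rather than the trial too small. The 80% belongs to the omnibus interaction, and a reader should not carry it over to the pairwise component contrasts.

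**What to change.** 1. In Statistical analysis, control the 5% level across the three primary interaction tests, for example with Holm, and run the Tukey or Games-Howell comparisons only for scores that pass. Alternatively, name one primary score and one primary time point.
2. In Sample size and power calculations, state the outcome and the number of occasions behind 147, and make that agree with the primary analysis. If the control in item 1 is used, report power with it and at more than one value of ε.
3. In the same section, say that 80% applies to the omnibus interaction. Add the difference it corresponds to at two occasions (about 0.43–0.49 SD) and the pairwise power at 49 per arm (about 64–78%).

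The cost is wording in the protocol and registry. Each primary test becomes somewhat stricter and the stated power slightly less favourable. If the primary analysis covers five occasions, no extra participants are needed under the stated inputs, although at ε = 0.7 and 134 completers power falls to about 75%. If it is pre-post on all three scores, a split leaves 66% at 147, so in that case naming a single primary score costs less.

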In sum, this study has several strengths. To the best of our knowledge, this is the first randomized dismantling intervention study for depression with the aim of exploring the contribution of a PPs component and the BA component in an Internet-based intervention. The three protocols are online interventions, helping to reach many people who need psychological treatments and would not otherwise have access to them. Furthermore, acceptability and usability measures will be included in order to assess the intervention’s feasibility and acceptance, in addition to an efficacy study. Finally, potential mediator mechanisms will be explored to identify the variables that lead to changes in depressive symptoms.

We are aware that this study has limitations. One of them is that the number of BA and PPs modules in the *IBAc* and *IPPc* is higher than in the *IGc*, although the clinical content is the same in the global protocol and in the protocols for the BA and PPs components. The reason for this is that the three protocols contain the same total number of modules (8 modules per each) and a similar number of words. We give all the patients the same amount of time to do the intervention to try to control this. Another limitation is that the dropout rates are expected to be high (around 30%) [103]. Efforts will be made to minimize the dropout rates by providing ICT and human support. Approaches to handling missing data will be considered and assessed using sensitivity analyses in order to apply the most robust and adequate method, based on both the missing data patterns and recommendations found in the literature (i.e., [87, 88]. In addition, difficulties in the recruitment phase will be considered.

In summary, this study extends the current literature about Internet-based interventions for depression. If positive results are achieved, they may have an important impact by providing better knowledge about the core elements of evidence-based treatments for depression.

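### The dropout allowance multiplies by 1.3 instead of dividing by 0.7, so 192 randomised leaves about 134, not 147, and power falls from 80% to about 76%

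*Protocol article*

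**What the plan says.** The section on sample size and power calculations in the protocol article bases the calculation on the interaction between intervention and measurement occasion. For the effect it says: "we assumed a proportion of explained variance of low magnitude for the interaction between the type of intervention and the measurement occasion, that is, 0.01". The other inputs are: "For a significance level of 5%, statistical power of 80%, assumed sphericity, and correlation of .7 between repeated measures". The result is 147 participants, 49 in each of three arms. The allowance for loss follows: "To this figure, an additional 30% was added to anticipate potential dropouts". The total is then 192, or 64 per arm. The software named is G*Power 3.1.9.2.

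The Discussion, in its paragraph on limitations, says what loss is expected: "the dropout rates are expected to be high (around 30" per cent).

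**The concern.** The 30% serves as two different quantities. In the Discussion it is a rate of loss among people who enter the trial. In the sample-size section it is a mark-up on the number who must remain at the end. These agree only when the rate is small. At 30% they differ noticeably, because losing 30% of an inflated total removes more people than the mark-up added.

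If so, the trial falls short of its own target number under its own dropout assumption, and readers will still take it to be an 80%-powered trial. All three arms are active and share half of their modules, so a null interaction is a realistic outcome. How such a result is read depends directly on the power the design really had.

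**Working it through.** **Inputs.** From the sample-size section: α = 0.05; target power 0.80; explained variance 0.01; correlation between repeated measures ρ = 0.7; sphericity; k = 3 equal arms; 147 needed; 192 randomised. From the Discussion: dropout of about 30%. The number of measurement occasions m used in the calculation is not stated and has to be inferred.

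**Step 1: reproduce 147.** For the within-between interaction in a repeated-measures ANOVA, as G*Power computes it:

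- f² = 0.01 / 0.99 = 0.0101
- noncentrality λ = f² × N × m / (1 − ρ)
- df1 = (k − 1)(m − 1), df2 = (N − k)(m − 1)
- power = P(noncentral F > F critical at α = 0.05)

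The smallest N with at least 80% power, by number of occasions:

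| m | smallest N |
|---|---|
| 2 | 147 |
| 3 | 121 |
| 4 | 104 |
| 5 | 92 |

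Only m = 2 gives the protocol's figure. At N = 147, λ = 0.0101 × 147 × 2 / 0.3 = 9.90 with 2 and 144 degrees of freedom, and power is 80.3%. Entering f = 0.10 instead of an explained variance of 0.01 gives 148. Noncentrality definitions without the correlation term give totals from 375 to 960. The stated 147 is therefore a two-occasion calculation.

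**Step 2: reproduce 192.**

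- Multiplying: 147 × 1.3 = 191.1, or 49 × 1.3 = 63.7 per arm, rounded up to 64, which makes 192.
- Dividing: 147 / 0.70 = 210, or 70 per arm.

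The stated total comes from multiplying.

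**Step 3: apply the expected dropout to 192.**

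- Remaining: 192 × 0.70 = 134.4, or 44.8 per arm.
- Shortfall: 147 − 134.4 = 12.6 participants with outcome data.
- Randomised participants missing: 210 − 192 = 18.
- Largest dropout that still leaves 147: 1 − 147/192 = 23.4%.

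**Step 4: power with those who remain (m = 2).**

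| N with data | λ | power |
|---|---|---|
| 147 | 9.90 | 80.3% |
| 135 | 9.09 | 76.5% |
| 134 | 9.02 | 76.2% |

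With f = 0.10, power at 134 is 75.7%. Solving for the explained variance that gives 80% power at N = 134 yields 0.0109, against the planned 0.010.

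**The case against.** Five points can be made for the plan.

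- **The effect is small.** It is similar to a slight change in an assumed input: with ρ = 0.68 instead of 0.70, power at 147 would be 77.5%, and with ρ = 0.72 power at 134 would be 79.2%. Both ρ and the explained variance are conventional values. This stands as a statement about size. It does not make the allowance correct, because the dropout step is plain arithmetic on figures the plan chose itself.
- **The 76% depends on two occasions, which the protocol never states.** The trial has five main assessments. By the same formula, 134 complete participants would give 84.6%, 90.6% and 94.5% power with three, four and five occasions. This stands as a condition on the 76%. But those designs would have required 121, 104 or 92 participants, so they are not the calculation reported. The shortfall against 147 needs no assumption about occasions.
- **The intention-to-treat analysis uses maximum likelihood with the EM algorithm, so dropouts are not discarded.** The article also does not say whether the 30% refers to leaving treatment or to missing assessments. This stands in part: 134 is an assumed number with outcome data. However, the Interventions section places the post-treatment assessment after completion of the eight modules, so many who stop treatment may lack it. A participant with baseline data only adds essentially nothing to a pre-post interaction. The per-protocol analysis is confined to completers in any case.
- **The sentence does literally what it says: 30% was added.** True, but its stated purpose is to cover dropout, and at the rate in the Discussion it does not.
- **80% is attached to 147, not to 192 with 30% loss.** That is correct. The fault lies in the allowance, and the power carried forward to the trial is overstated as a consequence.

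**Conclusion.** The concern holds. The allowance was computed as 147 × 1.3, whereas an expected 30% loss among those randomised requires 147 / 0.70 = 210. With 192 randomised, about 134 remain, and 147 is preserved only if dropout stays at or below 23.4%.

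Power for the planned effect is then about 76%, a loss of roughly 4 percentage points; equivalently, the explained variance detectable with 80% power rises from 0.010 to about 0.0109. The power figures assume the two-occasion interaction test that reproduces 147, the stated explained variance, correlation and sphericity, and that dropouts contribute no post-baseline information. The shortfall in numbers rests only on the stated 147, 192 and 30%. The error does not invalidate the trial, but the sample-size statement is wrong as written.

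**What to change.** Correct the sample-size section with one sentence in either of two forms:

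- with 192 randomised and 30% dropout, about 134 participants are expected to provide data, giving about 76% power for an explained variance of 0.01, or 80% power for about 0.011; or
- 192 randomised preserves the required 147, and so 80% power, only if dropout does not exceed about 23%.

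The same sentence should say that the calculation uses two measurement occasions, since these power figures depend on it.

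The cost is a slightly less favourable stated power. No additional enrolment is needed. If the sponsor prefers to keep 80% power at 30% dropout, the target becomes 210 (70 per arm), which is 18 more participants.
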